5.5 Intervention

The intervention process described fulfills the requirements suggested in the TIDieR checklist (Hoffmann et al., 2014). The TIDieR checklist involves a checklist and guide known as Template for Intervention Description and Replication (TIDieR) developed by an international group of experts and stakeholders to improve the completeness of reporting and ultimately the replicability of interventions (Hoffmann et al., 2014). All participants will receive an air purifier which may contain a High-Efficiency Particulate Absorbing (HEPA) filter for air purification (intervention) or not contain a HEPA filter (control).

The guideline for placing air purifiers in healthcare facilities for their effective functioning has been proposed by the Department of Health Government of Western Australia (2022). The air purifier will be placed in the room of each participating resident and positioned in the closest suitable proximity to the resident (point of source). There should be a minimum distance of ten centimetres between the equipment and the wall to ensure air circulation. To ensure free air flow of the air purifier, the air intake and outlet of the air purifier should be kept unhindered. There should be a clear space of at least 25 cm to the front of the air purifier. The air purifier will be positioned away from any heating or cooling sources, and it will be placed on a stable and solid surface.

The placement of air purifiers will be undertaken by one of the members of the research team who is responsible for collecting or determining outcome data. Communal and shared areas such as recreation rooms, lounges, dining areas, and double rooms will not contain an air purifier, as the study is seeking to determine the effect of air purifiers in an individual resident's room.

The first phase of the study will continue for three months. After the first phase of the study, a washout period of one week will be applied. Since the air purifier function is based on instant air

388 purification with the aid of HEPA filters, the chances of carryover effects are expected to be  
389 quite unlikely. Also, a long washout period may lead to missing data in the epidemiological peak  
390 of the trial phases, which may in turn further influence the outcome analysis. However, this  
391 period will be required to swap / change air purifiers between groups and for identifying and  
392 eliminating carryover effects, if any.

393 During the washout period, residents in the control phase will have their air purifier changed or  
394 modified and subsequently have an air purifier with HEPA filtration. Conversely, for residents  
395 who completed an intervention, they will have HEPA filtration removed in preparation for the  
396 control phase.

397 The person responsible for changing HEPA filtration will be a member of the research team who  
398 is not responsible for collecting or determining outcome data. The changeover process will  
399 occur in a way in which the resident remains blinded to the intervention. For example, a HEPA  
400 filter will not be removed or installed in view of a resident. These practices will ensure the  
401 double-blinding of the trial.

402 When air purifiers are moved between participants, they will be cleaned by a member of the  
403 research team in accordance with the manufacturer's instructions. External surfaces of the air  
404 purifier will be cleaned with a Therapeutic Goods Administration (TGA) registered disinfectant  
405 wipe with claims of activity against viruses and bacteria. There is no airborne transmission  
406 infection risk to residents with regards to moving air purifiers between residents (if this was  
407 required to be done).

408 The second phase of the study will continue for another three months.

409 **Fidelity**

410 The fidelity of the trial will be ensured by arranging random checks or observations made by the  
411 selection of nominated facility staff on the air purifiers and participants of the trial. These staff  
412 will have received training on the operation of air purifiers. They will check to identify if the air  
413 purifiers are turned on and to make sure that they are in active mode for their effective  
414 functioning. Minimum monthly checks like this will be carried out by the facility staff. In  
415 circumstances where an alert on the air purifier is identified, the member of the research team  
416 who is involved in the data collection will be notified immediately.

417 Regular checks on participants will also be done by the nominated staff member of the facility to  
418 estimate the time that participants spend outside the room to recognise the effectiveness of the  
419 intervention. This is important as it influences participants' exposure to the intervention and  
420 consequently, the outcome. For example, the air purifiers will be placed in the resident's room

and the duration of residents' exposure to air purifiers is a significant part of the study that may impact the outcome of the intervention. Any breakout period where there is a long gap in participants' exposure to air purifiers (such as spending outside the room for long hours, a day outing, days of leave, and hospitalisation) will be recorded by the nominated staff. This will be collected and recorded carefully by the member of the research team who is involved in data collection for it to be included in the outcome analysis for identifying the effectiveness of the intervention.

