### AND

- a clinician's judgement that the illness is due to an infection (European Centre for Disease Prevention and Control (ECDC), 2018). This definition is consistent with World Health Organization (WHO) Regional Office for Europe (2011).

An ARI will then be categorised as one of the following:

- ARI, no diagnostic test performed: Residents presenting with symptoms as identified by the definition of ARI and eligible to be categorized as an ARI case.
- ARI, influenza (A and B): Residents presenting with symptoms of ARI and confirmed influenza (A and B) by diagnostic lab tests.
- ARI, SARS Cov2: Residents presenting with symptoms of ARI and confirmed SARS Cov2 by institutional RAT or diagnostic lab tests.
- ARI, rhinovirus: Residents presenting with symptoms of ARI and confirmed rhinovirus by diagnostic lab tests.

- ARI, respiratory syncytial virus: Residents presented with symptoms of ARI and confirmed RSV by diagnostic lab tests.
- ARI, adenovirus: Residents presenting with symptoms of ARI and confirmed adenovirus by diagnostic lab tests.
- ARI, diagnostic test performed but no virus identified

Participants in the study will not be subject to a diagnostic test as part of the study. Any diagnostic tests will be determined as part of their medical care, facility procedure, or usual practice. We expect any ascertainment bias to remain constant throughout the study i.e., the same in both phases.

Secondary outcomes

The secondary outcomes of this study are:

- Time to first infection for participants. This will be defined as time in days since the commencement of the study phase to the diagnosis of ARI.
- The number of visits to an emergency department due to an ARI
- The number of hospital admission due to an ARI. A hospital admission is defined as being admitted to a hospital and having at least one overnight stay.
- The number of medical consultations including GP and NP reviews due to an ARI. A consultation will be defined as a billable visit to a medical or nurse practitioner and/or where a medical or nurse practitioner has documented an assessment related to an ARI in the participants' medical notes at the facility.

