## 5.9 Blinding

The study is double-blinded. The participant will be unaware of whether their air purifier contains a HEPA filter or not. The researcher determining the outcome (whether a participant has an ARI) will also be unaware of whether the participant has an air purifier with or without a HEPA filter. The procedure of changing the air purifiers will not involve any disclosure to participants or the researcher collecting outcome data about whether the air purifier has a HEPA filter. The

unblinding of the participant’s allocation to a treatment group will only occur immediately prior to the final analysis being undertaken.

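### Blinding of the facility nurses and clinicians who supply the primary outcome data is neither stated nor secured at the filter changeover

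*Protocol*

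**What the plan says.** Section 5.9 opens with "The study is double-blinded" and names whom this covers. Of the resident it says "The participant will be unaware of whether their air purifier contains a HEPA filter or not"; the other party is the researcher who decides whether an ARI occurred. Its sentence on changing the purifiers rules out disclosure to those same two parties.

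Section 5.5 has filters changed in the washout week by a team member with no outcome role. As an example of how the resident stays blinded, it says that a HEPA "filter will not be removed or installed in view of a resident. These practices will ensure the" double-blinding of the trial. Under Fidelity, trained facility staff check the units at least monthly. If they find an alert, the research-team member "who is involved in the data collection will be notified immediately".

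The outcome begins with facility staff. Section 5.6 requires, besides a symptom, "a clinician's judgement that the illness is due to an infection", and leaves testing to usual care. Section 5.10 draws the data from medical, clinical and nursing records and from verbal reports, including those of registered nurses. Section 6.1 says that the staff trained on the purifiers are registered or enrolled nurses.

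Section 5.8 describes the main safeguard: units are pre-labelled, those handing them out cannot see whether a filter is present, and the key is held by one researcher outside enrolment, data collection and outcome decisions.

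**The concern.** The outcome researcher visits fortnightly and works from what staff have written or say. Blinding that researcher cannot recover a symptom that was not charted, a test that was not requested or an infection that was not diagnosed. If some nurses or clinicians learn filter status, recording could differ between the filter and no-filter conditions, and the treatment comparison would carry that difference. In a two-period crossover, seeing a filter put in or taken out once reveals that resident's condition in both phases.

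Section 5.6 answers the ascertainment question by expecting any bias to be the same in both phases. That is a different condition. Each phase contains residents with and without filters, so recording can be equally complete in the two phases overall and still differ by filter status within each.

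**Working it through.** **Whom each step covers**

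- Sham unit, labels and concealed key (5.8): mask anyone who sees only the closed unit, facility staff included.
- Out-of-view rule for filter handling (5.5): stated for residents. Facility staff are not mentioned.
- No disclosure at changeover (5.9): participants and the researcher collecting outcome data. Facility staff are not mentioned.
- Device alerts (5.5): sent to the data-collecting member, who is meant to be blinded. The protocol does not say whether an alert can reveal filter status.
- Roles (5.5): units are placed by a member who is responsible for outcome data, while filters are changed by a member who is not. Placing a closed unit need not unblind anyone, but the two statements leave the separation of roles unsettled.

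**The protocol's own figure**

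Inputs from 5.7: discordant proportions 0.12 and 0.32, two-sided 5%, 80% power. These proportions equal 0.20 × 0.60 and 0.40 × 0.80, so they imply independence between a resident's two periods.

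- OR = 0.12/0.32 = 0.375.
- V = ¼(2/0.12 + 2/0.32) = 5.729.
- n per sequence = (1.960 + 0.842)² × 5.729 / (ln 0.375)² = 46.74, rounded up to 47, total 94.

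The stated sample size reproduces, and this point does not affect it.

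**Illustration with no true effect**

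True risk is 0.40 in both conditions, with independence and 47 per sequence as in 5.7. Control-phase ARIs are all recorded; a share of filter-phase ARIs is missed. That share is assumed, because the protocol gives none. With p the recorded filter-phase risk: a = p × 0.60, b = 0.40 × (1 − p), OR = a/b, V = ¼(2/a + 2/b), SE = √(V/47), and the rejection rate comes from z = ln(OR)/SE against ±1.96.

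| Filter-phase loss | p | a | b | OR | SE | Two-sided rejection |
|---|---|---|---|---|---|---|
| 0% | 0.40 | 0.240 | 0.240 | 1.00 | 0.298 | 5.0% |
| 5% | 0.38 | 0.228 | 0.248 | 0.92 | 0.299 | 5.9% |
| 10% | 0.36 | 0.216 | 0.256 | 0.84 | 0.301 | 8.7% |
| 20% | 0.32 | 0.192 | 0.272 | 0.71 | 0.307 | 20.5% |

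**The other direction**

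If the true risks are 40% and 20% and only 95%, 90% or 80% of control-phase ARIs are recorded, the same formulas give an OR of 0.41, 0.44 or 0.53 and power of about 73%, 65% or 45%, against 80% with full recording.

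These figures use the sample-size formula, not the mixed logistic model of 5.11, so they indicate scale only.

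**The case against.** A reader might infer that facility staff make the outcome and that the primary outcome is therefore unprotected. The protocol does not support that. Every participant has a unit, filter status is not visible from outside, and staff are given no access to the key, so they are masked unless someone opens a unit or handles a filter in front of them. Clinician judgement is one required element, but a blinded researcher determines whether there was an ARI. Section 5.9 places unblinding immediately before the final analysis.

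Three further arguments have force. The out-of-view rule is introduced as an example, so it need not be exhaustive. Section 5.5 allows units to be swapped as well as modified, and seeing a labelled unit exchanged reveals nothing. Nothing says that an alert differs by filter status; staff check that units are on and in active mode, which is not a filter check.

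The illustration also applies its loss to every filter-phase ARI. If 10% under-recording affected half the residents, or 20% a quarter of them, the average loss would be 5% and the false-positive rate about 6%.

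All of this limits the point without removing it. Default masking is not the same as the assurance in 5.5, staff are absent from every sentence on who is blinded, and alerts are sent to a person who should stay blinded. The reply in 5.6 about equality between phases does not address filter status.

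**Conclusion.** The point holds as a gap in stated and secured blinding. The groups whose judgement and records feed the primary outcome are not named as blinded, and the changeover procedure does not shield them. The listed practices do not by themselves ensure double-blinding. It would go too far to say that staff are unblinded, that alerts disclose filter status, or that the primary outcome is left unprotected.

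The size cannot be derived from the protocol. A 5% average loss barely moves the false-positive rate, to about 6%; a 10% loss gives about 9%, and a 20% loss about 21%. Both the degree and the direction of differential recording are assumptions. The change is worth making because the outcome is partly subjective and the remedy is cheap; confidence that the gap would matter in practice is moderate.

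**What to change.** - In 5.5 and 5.9, name facility nursing staff and treating clinicians as blinded.
- In 5.5, have the existing filter-changer make every filter change out of sight of staff as well as residents, and return closed units.
- Under Fidelity, send device alerts to the filter-changer or researcher 1 instead of the outcome data collector.
- Reconcile the two statements in 5.5 about who places units and who changes filters, saying for each role whether it may be combined with outcome work.
- In 5.6, restate the ascertainment assumption as equality between filter and no-filter conditions.

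The cost is protocol wording and a little more handling in the changeover week. No extra staff are needed, and the sample size and analysis do not change.

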## 5.6 Outcomes

### Primary outcome

The primary outcome is a reduction in the occurrence of ARIs. Each participant will have a binary outcome, no infection, and infection, for their control and intervention study period. The case definition for Acute Respiratory Infection (ARI) is the sudden/acute onset of at least one of the following four respiratory symptoms:

- cough
- sore throat
- shortness of breath
- coryza

### AND

- a clinician's judgement that the illness is due to an infection (European Centre for Disease Prevention and Control (ECDC), 2018). This definition is consistent with World Health Organization (WHO) Regional Office for Europe (2011).

An ARI will then be categorised as one of the following:

- ARI, no diagnostic test performed: Residents presenting with symptoms as identified by the definition of ARI and eligible to be categorized as an ARI case.
- ARI, influenza (A and B): Residents presenting with symptoms of ARI and confirmed influenza (A and B) by diagnostic lab tests.
- ARI, SARS Cov2: Residents presenting with symptoms of ARI and confirmed SARS Cov2 by institutional RAT or diagnostic lab tests.
- ARI, rhinovirus: Residents presenting with symptoms of ARI and confirmed rhinovirus by diagnostic lab tests.

- ARI, respiratory syncytial virus: Residents presented with symptoms of ARI and confirmed RSV by diagnostic lab tests.
- ARI, adenovirus: Residents presenting with symptoms of ARI and confirmed adenovirus by diagnostic lab tests.
- ARI, diagnostic test performed but no virus identified

Participants in the study will not be subject to a diagnostic test as part of the study. Any diagnostic tests will be determined as part of their medical care, facility procedure, or usual practice. We expect any ascertainment bias to remain constant throughout the study i.e., the same in both phases.

Secondary outcomes

The secondary outcomes of this study are:

- Time to first infection for participants. This will be defined as time in days since the commencement of the study phase to the diagnosis of ARI.
- The number of visits to an emergency department due to an ARI
- The number of hospital admission due to an ARI. A hospital admission is defined as being admitted to a hospital and having at least one overnight stay.
- The number of medical consultations including GP and NP reviews due to an ARI. A consultation will be defined as a billable visit to a medical or nurse practitioner and/or where a medical or nurse practitioner has documented an assessment related to an ARI in the participants' medical notes at the facility.

5.7 Sample size

An estimate of a 50% reduction in ARI by keeping 40% as the current incidence rate requires a 40% respiratory infection proportion in the control group and a 20% proportion in the treatment group. For the AB-BA sequence of the crossover trial, the required number of participants will be 94 in total i.e., 47 for the AB sequence and another 47 for the BA sequence.

Assuming the proportion of respiratory infections under control conditions is 40% and the expected proportion of respiratory infections is 20% when using air purification, a cross-over trial with 94 participants (47 in each sequence) will have 80% power to detect this difference at the 5% significance level. This corresponds to an odds ratio of 0.375 for air purification (filtration) vs control (no filtration). The calculation of sample size has been illustrated in figure.2.

Calculate

Design

Reports

Plots

Plot Text

Solve For: Sample Size

Test

Alternative Hypothesis: Two-Sided

Power and Alpha

Power: 0.8

Alpha: 0.05

Effect Size

Odds Ratio

Input Type: Proportions

Pt (Treatment Proportion|H1): 0.2

Pc (Control Proportion): 0.4

Standard Deviation of Log(Odds Ratio)

Estimation Method: Use Estimated Discordant Cell Proportions

Discordant Cell Proportions:

p01(1): 0.12

p01(2): 0.32

p10(1): 0.32

p10(2): 0.12

2x2 Cross-Over Design Annotations

Odds Ratio = OR = Ot/Oc = [Pt/(1-Pt)] / [Pc/(1-Pc)] or  $\sqrt{[P01(1)P10(2) / P10(1)P01(2)]}$

SEQUENCE 1 (C→T):

Period 2 (Trt)

Yes

No

Total

Period 1 (Ctrl)

Yes

P11(1)

P10(1)

Pc(1)

No

P01(1)

P00(1)

1-Pc(1)

Total

Pt(1)

1-Pt(1)

1

SEQUENCE 2 (T→C):

Period 2 (Ctrl)

Yes

No

Total

Period 1 (Trt)

Yes

P11(2)

P10(2)

Pt(2)

No

P01(2)

P00(2)

1-Pt(2)

Total

Pc(2)

1-Pc(2)

1

Figure: 2. Sample size calculation of the proposed project

The assumptions for the proportions of participants with a respiratory infection are based on data from a systematic review (Childs et al., 2019). It is now widely accepted that respiratory viruses are transmitted via aerosols and that transmission via inanimate surfaces is not very common and for some respiratory pathogens, such as SARS-COV2, potentially negligible (Greenhalgh et al., 2021; Tang et al., 2021). Therefore, if a person has clean air the likelihood of transmission is negligible and improving air quality is likely to have a significant role in reducing risk of infection. There have been several studies that support the use of air purification as a way to reduce the risk of respiratory infections.

- In a COVID-19 ward, 99% of aerosols were cleaned within 5 minutes, by use of an air purifier (Busing et al., 2022).
- Simulation studies, including one on a classroom where the use of an air purifier was found to have 70-90% reduction in transient aerosols (Burgmann & Janoske, 2021)

Given the topic, there have been no RCTs or quasi-experimental studies that have examined reductions in patient outcomes (respiratory infection) when using air purifiers. In part, this is why

Research protocol, version 2.0 24.01.2023

Page | 17

this study is critical. With the above justification and context in mind, we have also relied on expert opinion when determining the 50% reduction figure. These have included those from a range of disciplines – infectious disease, infectious control and aerosol science. Expert opinion includes people who have advised national government on Australia’s pandemic response. Please also note that in our sample size estimate, we have also been conservative with the baseline incidence rate, which is likely to be higher.

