283 will be obtained from the relevant person with the authority to provide consent on behalf of the  
284 resident (Commonwealth Department of Health and Aged Care, 2015). The potential  
285 participants’ guardians will be encouraged to discuss the research with the potential participant  
286 if the participants are able to understand what the study involves, based on their level of

287 cognitive impairment. Then it should be a joint discussion on whether the individual should  
288 participate in the study or not.

289 Participation in this study is entirely voluntary. This means that the participants do not need to  
290 agree to take part in the research, and participants' or their guardians' refusal to take part will  
291 also be respected. If any party decides to take part, they can still withdraw from the study at any  
292 time without having to give reasons for their choices/decisions. In such circumstances, any data  
293 collected concerning participants, or their guardians will be withdrawn from the study. Whatever  
294 the decision may be, the participants will be assured that it will not affect their treatment or  
295 relationship with the staff of the facility who are caring for the participants. Of the people caring  
296 for the participants, only the nursing staff and the members of the research team will be aware  
297 of participation or non-participation.

298 Potential participants who meet the eligibility criteria will be provided with information about the  
299 study. A member of the research team will follow up with potential participants to determine their  
300 interest in participating in the study. The follow-up period will be at least 3 days post-initial  
301 contact to allow participants time to consider participation.

302 Sometimes during the course of a study, new information becomes available about the  
303 treatment that is being studied and the participants will be kept informed of any significant new  
304 findings which may affect their willingness to continue in the study.

305 In circumstances where the potential participants require public guardians' approval since they  
306 are unable to provide consent, they will be excluded from the study.

307 In the enrolled facilities, a member of the research team will provide information to residents or  
308 their guardians about the study in paper forms. This will include the study requirement for  

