613 research for strengthening the value of the research data for future research (The University of  
614 Newcastle (UON), 2017). The ethical protocols of HREC (UON) in relation to privacy,  
615 confidentiality, and data protection will be abided by.

616

617 **5.11 Data analysis**

618 Descriptive statistics of the sample will report demographics and clinical characteristics stratified  
619 by treatment order. An alpha threshold of 0.05 will be used to assess statistical significance and  
620 the reported results will include 95 % confidence intervals. Due to the high likelihood of  
621 participants being lost-to-follow-up in this sample, demographics and clinical characteristics will  
622 be used to conduct the analysis using multiple imputations.

623 **Primary outcome**

624 The effectiveness of treatment will be assessed by comparing the proportion of infections over  
625 the two cross-over study periods. Each participant will have a binary outcome, no infection, and  
626 infection, for their control and intervention study period and analysis will include fixed effect for  
627 each site. The treatment effect will be measured using logistic regression mixed effects models,  
628 where the main effects in the model will be treatment, study collection time, and cross over  
629 design characteristics. A random intercept effect for an individual will correct for non-  
630 independent observations made between the cross over study periods. The model will estimate  
631 an odds ratio that will compare the odds of infection when having air filtration active against not  
632 having air filtration active.

633 As the mean incubation and infectious period for common respiratory viral pathogens is less  
634 than 7 days, a 1-week washout period will be sufficient within this study. Where a person

acquires an infection during a phase, the infection will be attributed to that phase (noting that we are measuring infection as a dichotomous variable). Because our measurement of infection is a dichotomous variable, symptoms must resolve before a new infection can be counted.

Secondary outcome

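### The 80% power stated for 94 participants assumes 94 complete pairs and makes no allowance for the loss to follow-up that the protocol itself expects

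*Protocol*

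**What the plan says.** Section 5.7 gives 94 as the total required, 47 per sequence, and concludes that "a cross-over trial with 94 participants (47 in each sequence) will have 80% power to detect this difference at the 5% significance level". The inputs shown there are "Alternative Hypothesis: Two-Sided", "Pt (Treatment Proportion|H1): 0.2" and "Pc (Control Proportion): 0.4", with alpha 0.05 and power 0.8. The standard deviation of the log odds ratio is taken from discordant cell proportions of 0.12 and 0.32. There is no dropout term among the inputs, and no inflated enrolment figure anywhere in the protocol. The same power statement is repeated in section 5.11, at the end of the paragraph on the secondary outcome.

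Four other places bear on completeness:

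- Section 5.11, opening paragraph, gives as its reason for multiple imputation the high likelihood of "participants being lost-to-follow-up in this sample, demographics and clinical characteristics will" be used in the imputation. No rate is given.
- Section 5.11, secondary outcome, treats loss to follow-up and death as censoring events.
- Section 5.3 says that, on withdrawal, any data "collected concerning participants, or their guardians will be withdrawn from the study". Section 8.1 says the same but excepts data already in the study database or analysis, which may be kept.
- Section 6.1 withdraws a participant if the purifier continues to cause distress.

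**The concern.** A discordant pair exists only when both phases of the same person are observed. A sample size built on discordant cells is therefore a count of people who complete both phases. Section 5.7 presents it as the number of participants, while section 5.11 plans for substantial loss among aged-care residents followed for about six months. The two statements do not fit together unless something absorbs the loss, and the protocol does not say what does.

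At stake is how a null result is read. Section 5.7 says there are no earlier randomised or quasi-experimental studies with infection outcomes, so a non-significant result from a trial described as having 80% power could carry more weight against the purifier than it should.

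**Working it through.** **1. Reproduce the stated figure.** Inputs from section 5.7: two-sided alpha 0.05 (z = 1.960), power 0.80 (z = 0.842), discordant cells 0.12 and 0.32 (mirrored between sequences), odds ratio (0.2/0.8)/(0.4/0.6) = 0.375. The cells give the same odds ratio: √(0.12 × 0.12 / (0.32 × 0.32)) = 0.375.

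- Var(log OR) = ¼ × 2 × (1/0.12 + 1/0.32)/n = 5.729/n, with n complete pairs per sequence.
- ln 0.375 = −0.981, squared 0.962.
- n = (1.960 + 0.842)² × 5.729/0.962 = 7.849 × 5.729/0.962 = 46.74, rounded up to 47; total 94.
- Power at n = 47: SE = √(5.729/47) = 0.349; 0.981/0.349 = 2.809; Φ(2.809 − 1.960) = 0.802.

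The calculation is correct. The only slack in 94 is rounding.

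**2. Same formula with fewer complete pairs.** The protocol gives no loss rate, so 10%, 20% and 30% are assumed.

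| Not completing both phases | Complete pairs | SE of log OR | Power |
|---|---|---|---|
| 0% | 94 | 0.349 | 80% |
| 10% | 85 | 0.367 | 76% |
| 20% | 75 | 0.391 | 71% |
| 30% | 66 | 0.417 | 65% |

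With 75 pairs, independent phases and a control risk of 40%, 80% power requires a treated risk of about 17.5%, a 56% reduction instead of the planned 50%. Put in participants, keeping 94 completers would take 94/0.9 = 105, 94/0.8 = 118 or 94/0.7 = 135 enrolled (rounded up).

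**3. The planned analysis.** Section 5.11 specifies a mixed-effects logistic model with a random intercept, which also uses people observed in one phase only. The protocol's cells imply no within-person correlation: 0.4 × 0.8 = 0.32 and 0.6 × 0.2 = 0.12. On that assumption, logistic regression on treatment and period, without the random intercept, was simulated. As a closed-form check, the two-proportion formula with m observations per condition is

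Φ[(0.2√m − 1.960√(2 × 0.3 × 0.7)) / √(0.24 + 0.16)].

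If a fraction d is lost entirely, m = 94(1 − d). If it is lost only before phase 2, m = 94(1 − d/2).

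| d | Lost entirely: simulated | Closed form | Lost only before phase 2: simulated | Closed form |
|---|---|---|---|---|
| 0% | 86% | 85% | 86% | 85% |
| 10% | 83% | 82% | 85% | 84% |
| 20% | 77% | 77% | 80% | 82% |
| 30% | 71% | 71% | 79% | 79% |

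Repeat simulations moved these entries by about one or two percentage points, so they should be read as approximate.

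**4. Imputation.** Section 5.11 imputes from demographics and clinical characteristics. This can reduce bias from selective loss. It does not supply the infection outcome of an unobserved phase, so it does not bring the information back to that of 94 complete pairs.

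**The case against.** The strongest reply is that the primary analysis is not a discordant-pair test. On the protocol's own cells, the logistic model starts at about 86% power with full completion, and moderate loss may leave it near or above 80%. This stands. A reader might infer from section 5.7 that 80% power is reached only if every participant completes both phases. That is true of the stated calculation, but the documents do not support it for the planned model. The reply is not a full answer either: the protocol does not use it to justify 94, it rests on zero within-person correlation and on leaving out the random intercept, and it fails at 20% loss if those participants' data are removed entirely.

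Nor can one assume that everyone who leaves loses all their data. Section 5.3 reads that way for withdrawal, but section 8.1 makes an exception for data already entered, and death or other loss is not withdrawal of consent. Hence the two loss patterns in the working.

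Section 5.7 also calls the baseline conservative and likely to be higher. A 50% risk halved to 25% would give 83% power with 75 pairs by the same formula. But no amount is stated, and it is not offered as an allowance for loss.

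A reader might also take the wording "An estimate of a 50% reduction in ARI by keeping 40% as the current incidence rate" to mean that 40% is a rate over a longer period, so that the three-month risk, and the power, are much lower. The documents do not give the period. Section 5.7 goes on to use 40% as a proportion under control conditions, and section 5.6 defines the binary outcome per study period. That reading cannot be established here and forms no part of this point.

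Finally, section 5.11 requires 95% confidence intervals, which will show the precision achieved and limit over-reading of a null result.

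**Conclusion.** The arithmetic behind 94 is right; what it is said to deliver is incomplete. The 80% belongs to 94 people observed in both phases, and the protocol expects not to have them. By the stated method, the shortfall is about 4, 9 or 15 percentage points at 10%, 20% or 30% non-completion. Under the planned type of model with uncorrelated phases, power stays at about 80% or more at 10% loss in either pattern. At 20% it is about 77% to 80%, and at 30% about 71% to 79%, depending on whether phase 1 data are kept. The true size depends on three things the protocol does not state: the loss rate, the within-person correlation, and which data of those lost are kept. It is therefore not shown that the trial falls below 80% under its planned analysis. What is shown is that the 80% claim is unsupported at the loss the protocol anticipates. This should be fixed; it does not undermine the design.

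**What to change.** Keep 94. In section 5.7, and in the copy in section 5.11:

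- Say that the 80% assumes 94 participants with both phases observed.
- State an expected loss rate and its basis.
- Restate the power, or the detectable difference, at that loss.
- Name the method behind the restated figure: the complete-pair formula (about 76%, 71% and 65% at 10%, 20% and 30%) or the planned mixed model. If the mixed model, give the within-person correlation assumed.
- Say whether phase 1 data of those lost are kept, consistently with sections 5.3 and 8.1.

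The cost is protocol wording and a short recalculation. No extra participants and no change of design or analysis are needed. The stated power may become less favourable.
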